## Abstract

Metabolic dysfunction and excess accumulation of adipose tissue are detrimental side effects from breast cancer treatment. Diet and physical activity are important treatments for metabolic abnormalities, yet patient compliance can be challenging during chemotherapy treatment. Time-restricted eating (TRE) is a feasible dietary pattern where eating is restricted to 8 h/d with water-only fasting for the remaining 16 h. The purpose of this study is to evaluate the effect of a multimodal intervention consisting of TRE, healthy eating, and reduced sedentary time during chemotherapy treatment for early-stage (I–III) breast cancer on accumulation of visceral fat (primary outcome), other fat deposition locations, metabolic syndrome and cardiovascular disease risk (secondary outcomes) compared with usual care. The study will be a two-site, two-arm, parallel-group superiority randomised control trial enrolling 130 women scheduled for chemotherapy for early-stage breast cancer. The intervention will be delivered by telephone, including 30–60-minute calls with a registered dietitian who will provide instructions on TRE, education and counselling on healthy eating, and goal setting for reducing sedentary time. The comparison group will receive usual cancer and supportive care including a single group-based nutrition class and healthy eating and physical activity guidelines. MRI, blood draws and assessment of blood pressure will be performed at baseline, after chemotherapy (primary end point), and 2-year follow-up. If our intervention is successful in attenuating the effect of chemotherapy on visceral fat accumulation and cardiometabolic dysfunction, it has the potential to reduce risk of cardiometabolic disease and related mortality among breast cancer survivors.

Breast cancer is the most commonly diagnosed malignancy in women worldwide, representing 25 % of annual new cancer cases^(1)^. In Canada, mortality for early-stage breast cancer has decreased by 48 % over the past 40 years, with a concurrent emergence of competing risks from non-cancer causes. For example, breast cancer survivors are at an increased risk for weight gain, obesity^(2)^, hypertension, type 2 diabetes^(3,4)^, heart failure and cardiovascular disease (CVD)-specific mortality^(5)^ compared with the general population.

The direct toxic effects of breast cancer treatment on the heart (cardiotoxicity) are well characterised as a contributor to elevated CVD risk^(2)^. However, metabolic dysfunction, characterised as insulin resistance, dyslipidemia and adipose tissue (AT) (fat) accumulation, is emerging as an important potential consequence of breast cancer treatment^(6)^. In non-cancer populations, metabolic syndrome, a cluster of three or more of dyslipidemia, hypertriacylglycerolaemia, abdominal obesity, hyperglycaemia and hypertension, is associated with a 2-fold increased risk of CVD^(7)^. An observational study found that chemotherapy treatment for breast cancer resulted in the new development of metabolic syndrome in 73 % of women^(8)^. Among all women in the observational study, there was a 108 % increase in insulin resistance and a 32 % average increase in inflammation during chemotherapy. In long-term follow-up, each criterion of metabolic syndrome was significantly worsened between end of chemotherapy and the 4–5-year follow-up period^(9)^. Evidence of various forms of metabolic dysfunction persisting at 5–30 years after chemotherapy treatment has also been reported^(10,11)^. Thus, metabolic toxicity from chemotherapy may represent an underappreciated contributor to the elevated CVD risk among breast cancer survivors.

Excess accumulation of fat within ectopic regions (e.g. visceral, intermuscular, or hepatic) triggers adverse metabolic effects and inflammation. In non-cancer populations, ectopic fat is more strongly linked to CVD risk than the total quantity, which is dominated by subcutaneous fat^(12)^. At the time of breast cancer diagnosis, the volume of visceral and intermuscular but not subcutaneous fat are linearly associated with CVD events within 6 years of follow-up, even among those with normal BMI and after adjustment for pre-existing CVD risk factors and treatment type^(13)^. Further, chemotherapy for breast cancer results in rapid (within 2–3 months) and persistent (≥1 year) accumulation of visceral and intermuscular fat^(14–16)^.

Diet and physical activity interventions play important roles in the treatment of metabolic abnormalities and body composition. Intermittent fasting is a pattern of eating involving voluntary abstinence from food alternated with periods of *ad libitum* eating (unrestricted amount and content). A variety of intermittent fasting formats have been examined during chemotherapy for breast cancer and have shown promise as safe interventions with positive effects on quality of life and treatment toxicity in women undergoing chemotherapy for breast cancer^(17)^. Time-restricted eating (TRE) is a form of intermittent fasting that involves *ad libitum* energy intake within a set window of time, commonly 8 h, followed by 16 h of fasting (16:8 TRE) daily. To our knowledge, TRE has not been studied during chemotherapy but shows promise as a feasible and effective therapy to mitigate metabolic toxicity from chemotherapy.

TRE has positive cardiometabolic health effects, including reduced body fat (whole body, visceral, liver and intermuscular^(18–22)^, inflammatory markers (IL-6 and TNF-*α*), adipokines (leptin and adiponectin), and improved lipid profile, fasting glucose, insulin sensitivity, and blood pressure^(18,19,23)^. TRE is also feasible, with adherence typically > 85 % among adults with obesity, metabolic syndrome or diabetes^(18)^. We recently demonstrated feasibility, safety and participant acceptability of 8 weeks of TRE in breast cancer survivors 3 years post-chemotherapy^(24)^. Our intervention also resulted in a 5 % reduction in visceral fat, a 1·0 kg decrease in whole-body fat mass, and a 15 % relative reduction in the Framingham 10-year CVD risk score^(24)^.

Appropriate nutrition and healthy eating practices can also reduce the burden of chemotherapy symptoms and improve health across the cancer continuum. Dietary intake and physical activity are inextricably linked to cardiometabolic disease risk through reciprocal contributions to energy balance and obesity. Outside of sleep, time spent not being physically active is considered sedentary time, defined as any waking behaviour done while sitting, reclining or lying down that expend ≤ 1·5 metabolic equivalents. Sedentary time has consistently shown to be higher in cancer survivors than controls^(25,26)^. Recently, we found that within the year after starting chemotherapy for breast cancer, whole-body and visceral fat accumulation were associated more strongly with an objectively measured increase in sedentary time (*r* = 0·47 & 0·51, respectively, both *P* < 0·001, unpublished) than either moderate-intensity physical activity or cardiorespiratory fitness, which are the focus of current exercise guidelines for cancer patients. These findings demonstrate a need for alternative approaches to energy balance during chemotherapy for early-stage breast cancer to attenuate fat accumulation.

The purpose of the Impact of Metabolic health Patterns And breast Cancer over Time in Women (IMPACT-Women) trial is to evaluate the effect of a multimodal behavioural intervention involving TRE, healthy eating and reduced sedentary time on ectopic AT and cardiometabolic profile *versus* usual cancer care in women receiving chemotherapy treatment for early-stage (I–III) breast cancer. We hypothesise that the intervention will attenuate ectopic AT, markers of metabolic dysfunction and CVD risk, and chemotherapy symptoms. Our secondary hypothesis is that the intervention effects on the cardiometabolic profile and incident diagnoses will persist to a 2-year follow-up.

## Methods

### Study design, randomisation and blinding

IMPACT-Women is a two-site, two-arm, parallel-group superiority randomised controlled trial. Participants will be randomised 1:1 to the two groups using permutated blocks with random block sizes of two and four, stratified by study site, chemotherapy type (adjuvant/neoadjuvant), and postmenopausal status (yes/no). Randomisation will occur after completion of baseline assessments using a blinded online electronic randomisation tool, with enrolment and assignment performed by a research coordinator. All outcome assessors will be blinded to group assignment. Blinding participants to a behavioural intervention is not possible but is not expected to bias our physiological outcomes. Participants’ treating oncologists will not be blinded as we expect that group assignment may need to be discussed during care.

### Ethics approval and registration

Both sites provide independent research ethics approval (HREBA.CC-22–0128; CAPCR.22–5374), which will be amended with protocol modifications. All participants will provide written informed consent. The trial is registered with clinicaltrials.gov (registration #NCT05432856).

### Participant eligibility

We will recruit adult females (≥ 18 years) diagnosed with early-stage (I–III) breast cancer who will receive any type of neoadjuvant (pre-surgical) or adjuvant intravenous chemotherapy. Individuals without access to a cellphone with Bluetooth capability (required for intervention adherence tracking) will be excluded. We will exclude individuals who have type 1 diabetes and type 2 diabetes if hemoglobin A1c > 10 % or are taking insulin or sulfonylureas. For safety reasons, we will also exclude participants with research MRI contraindications (e.g. pacemaker, pregnancy, and magnetic implants), a self-reported history of an eating disorder, BMI < 18·5 kg/m^2^ or clinical signs of cachexia (oncologist’s discretion) or who are otherwise lacking oncologist’s approval, ≥ 5 % weight loss within the last 6 months, and uncontrolled thyroid disorder. Individuals with a BMI > 40·0 kg/m^2^ will be excluded as a threshold to confirm body habitus fit within the MRI scanner bore. Those reporting currently working night/rotating shifts, eating within ≤10-hour window or consistently eating less than three meals per d in the past 3 months will be excluded because of the potential impact on the TRE intervention. Finally, we will exclude patients who cannot communicate in English or do not have medical clearance to perform maximal exercise testing.

### Participant recruitment

We anticipate that recruitment will start in January 2023 and be completed by December 2024. We will recruit from two Canadian university-affiliated cancer hospitals: the Princess Margaret Cancer Centre and the Cross Cancer Institute. At both sites, recruitment will be facilitated by the breast medical oncology circle of care who will request consent for contact by the research coordinator, who will screen and consent participants.

### Intervention

The intervention period will start shortly after randomisation and continue until the participant has completed all post-chemotherapy outcome assessments that occur 2–6 weeks after the last treatment (Fig. 1). The intervention is designed as a multimodal approach to improve metabolic health and will consist of:

**Fig. 1. f1:**
[figure not shown]
Intervention and follow-up diagram.

#### Time-restricted eating

Participants will be asked to follow 16:8 TRE, but with flexibility incorporated to personalise the protocol to adapt to the dynamic nature of treatment symptoms, as well as their lifestyle, or preferences. TRE parameters can vary within the following pre-specified and evidence-based rules shown to improve cardiometabolic health: (1) adjustment of eating window length from 8 h up to 10 h; (2) self-selecting their eating window start time as long as end time is > 3 h before bedtime; (3) follow TRE as many days possible, but if time off is required, aim to limit it to 1–2 d off following at least five successive days each week.

#### Healthy eating

A registered dietitian will provide participants with a copy of Canada’s Food Guide, pre-determined nutritional education based on Canadian dietary guidelines, oncology guidelines for protein intake, individualised counselling and recommendations, and goal setting to promote healthy eating and overall nutritional well-being.

#### Sedentary time reduction

Both environmental and educational strategies will be incorporated to reduce sedentary time. Study staff will provide participants with the Canadian 24-h movement guidelines (which encompass recommendations for sedentary behaviour, physical activity and sleep), as well as education on sedentary time and the associated health impacts, counselling and goal setting on strategies to reduce sedentary time throughout the intervention period. All participants will receive a Fitbit physical activity tracker to enable tracking of daily step counts, reminders to move after periods of sedentary behaviour, and goal setting related to these activities. Goals will be reviewed and progressed throughout the intervention.

#### Intervention delivery

All components of the intervention will be delivered remotely by phone via evidence-based self-regulatory health behaviour support techniques^(27)^ including provision of education, ongoing tailored feedback, self-monitoring tools and goal setting. Participants will receive: (1) one-on-one 30–60-minute phone calls with a registered dietitian shortly after randomisation (week 0), and at 1, 3, 6, 10, 15, and 21 weeks and (2) daily self-monitoring via twice daily automated text messages about eating times and provision of a Fitbit physical activity tracker. At week 0, the registered dietitian will explain the rationale for TRE, including the pre-specified rules and provide instructions for starting TRE that evening. They will also review the participant’s baseline Fitbit data with them, provide initial education on sedentary time and introduce strategies to reduce sedentary time. Strategies to reduce sedentary time will include breaking up periods of sedentary time and a goal of increasing their daily step count between calls. At the follow-up support calls, feedback on TRE and sedentary time reduction adherence and counselling on barriers to adherence will occur. Potential symptoms and adverse events will be systematically tracked at these phone calls. The intervention focus on healthy eating and overall nutritional well-being will start in week 3 with an individualised assessment of dietary intake, education on Canada’s Food Guide and an individualised goal setting towards healthy eating. Since muscle loss is the primary nutrition problem that people with cancer experience, our nutrition intervention will focus on the protein intake recommendations from oncology nutrition guidelines^(28)^. In subsequent support calls, the registered dietitian will provide nutrition education, review success in achieving individualised nutrition goals, provide new goals as needed, and discuss barriers to behaviour change.

### Comparison group

The comparison group will receive the current standard of cancer and supportive care at our institutions including a single group-based ‘nutrition during cancer treatment’ class, a copy of Canada’s Food Guide, the Canadian 24-h movement guidelines and a Fitbit tracker. The control group will be instructed to maintain their usual dietary habits (timing, amount and type) outside of any recommendations given in the nutrition class for the duration of the intervention period. The research coordinator will perform the same number and timing of phone calls for participants in the comparison group as that in the intervention group to control for social support, to track the self-reported eating window to assess contamination and to collect adverse events.

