#### Safety outcomes

We will provide all participants with a Fibit body weight smartscale at baseline to take home to measure their weight first thing in the morning at least every 3 weeks. Based on global malnutrition guidelines^(29)^, if participants experience weight loss of 2 % or greater since their last weigh in, a registered dietitian will follow up with the participants to screen for the possible cause of weight loss and provide nutrition education and goals to minimise further weight loss. A 1-week follow-up will be scheduled to evaluate further weight changes. The participant’s treating oncologist will be notified if the participant continues to lose weight at the 1-week follow-up, or if weight loss at any 3-week weight check-ins exceeds 5%. Selected CTC-AE relevant to nutritional impact will be evaluated during the intervention at each of the support phone calls and through patient medical records collected via standard of care. At the support calls, participants will be asked if they have experienced each adverse event. If they respond positively, they will be further probed to ascertain the severity/grade and origin of the adverse event, and if relevant, the duration. Due to very low risk of major adverse events from our intervention, study investigators will assess safety outcomes on a case-by-case basis in lieu of a data safety monitoring committee.

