Our intervention is designed to address potential barriers to adherence common among patients receiving active cancer treatment. For example, we incorporated guidelines that allow participants to deviate from strict TRE in ways that are still supported by evidence for cardiometabolic health effects, including altering the length of TRE, selecting the start time of their eating window and guidance for taking a day off from TRE when required. Accounting for personal preferences in health interventions has been found to enhance recruitment and foster participant autonomy, enjoyment, and intervention adherence^(45,46)^. To overcome the common barrier of added study visits on top of extensive medical appointments, the intervention is delivered by phone, and in-person outcome assessments are only required three times over 2 years. This remote delivery format also increases potential for widespread implementation and future scalability to health systems and more remote communities. We will disseminate study results through academic conferences, peer-reviewed publications, and targeted patient and clinician events (e.g. survivorship groups and Grand Rounds).

A strength of this study is the use of 3T MRI as a non-invasive, safe (no ionising radiation), and highly reproducible technique to quantify the primary outcome (visceral AT), and other ectopic AT pools in the liver and thigh muscles. Our study will provide novel additions to the emerging evidence that rapid expansion of ectopic AT pools and their associated metabolic and/or cardiovascular dysfunction during breast cancer treatment plays a central role in the increased risk of CVD events among breast cancer survivors.

We have taken steps to minimise potential sources of bias. While blinding participants and their care team is not possible due to behavioural nature of the intervention and for patient safety, all outcome assessors will be blinded to the group assignment. In addition, participants in the comparison group will receive the same number and timing of calls to control for social impact and to assess contamination. One limitation is that we are using a parallel study design to implement a multimodal intervention which limits our ability to determine the individual effects of each component of the intervention.

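### Call-collected adverse events are elicited by a different, unblinded role in each arm, so the blanket assessor-blinding statement does not cover them and their between-arm summary risks differential ascertainment

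*Protocol article*

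**What the plan says.** Under Study design, randomisation and blinding, the protocol article states "All outcome assessors will be blinded to group assignment", with no exception. The Discussion repeats it among the steps taken against bias: "all outcome assessors will be blinded to the group assignment".

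Safety is listed in the Outcomes section, to be judged by malnutrition guidelines and selected CTC-AE version 5 terms on nutrition and muscle mass. It also has its own subsection, headed Safety outcomes.

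Collection by phone is described separately for each arm:

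- **Intervention arm (Intervention delivery).** Participants receive "phone calls with a registered dietitian shortly after randomisation (week 0), and at 1, 3, 6, 10, 15, and 21 weeks". On safety: "Potential symptoms and adverse events will be systematically tracked at these phone calls".
- **Comparison arm (Comparison group).** "The research coordinator will perform the same number and timing of phone calls for participants in the comparison group". The stated purposes are to control for social support and "to track the self-reported eating window to assess contamination and to collect adverse events".

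The Safety outcomes section says that participants are asked about each listed event at the support calls and that, after a positive answer, "they will be further probed to ascertain the severity/grade and origin of the adverse event". It names medical records as a second source of these events.

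**The concern.** The person who asks about adverse events differs systematically by arm. In one arm it is a nutrition professional who is counselling on the intervention. In the other it is a coordinator who is not delivering it. The terms collected are mainly nutritional, which is where the callers' training is most likely to change what is recognised and followed up. Neither caller can be blind to the arm, because each role phones one arm only.

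Two things are at stake. The first is accuracy: the blinding statement, offered to readers as protection against bias, is not true of this group of outcomes. The second is interpretation. The authors say that, to their knowledge, time-restricted eating has not been studied during chemotherapy, so readers will look to the arm-wise adverse-event summary. A difference in call-collected events, or the lack of one, could partly reflect who asked. A larger sample would not remove that.

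**Working it through.** The plan gives no figure on this point, so there is none to reproduce. The main check sets the sections side by side.

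1. **Are adverse events outcomes?** Yes. Safety appears in the Outcomes section and again under the heading Safety outcomes.
2. **Who elicits them in the intervention arm?** The tracking sentence in Intervention delivery refers back to the support calls, and those calls are with the registered dietitian.
3. **Who elicits them in the comparison arm?** The research coordinator, named in Comparison group.
4. **Do the callers know the arm?** Yes. The dietitian is counselling on the intervention, and the coordinator's calls are to comparison participants. The blinding section also has "with enrolment and assignment performed by a research coordinator".
5. **What is matched between arms?** The number and timing of calls. Caller role and call content are not matched.
6. **Does the blinding statement hold for these data?** No. Steps 1 to 4 conflict with an unqualified claim about all outcome assessors.

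**Illustration of size (assumed values).** Let π be the true proportion with an event, the same in both arms, and d₁ and d₂ the proportions of events detected in each arm. The observed proportions are a = π·d₁ and b = π·d₂, so the spurious difference is π(d₁ − d₂).

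With n = 65 per arm (Sample size section), the chance of a significant result in that direction at two-sided 5% is approximately Φ[((a − b) − 1.96·SE₀)/SE₁]. Here SE₀ = √(2p̄(1 − p̄)/n), with p̄ the mean of a and b, and SE₁ = √((a(1 − a) + b(1 − b))/n).

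Worked case, π = 0.40, d₁ = 0.90, d₂ = 0.70:

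- a = 0.40 × 0.90 = 0.36; b = 0.40 × 0.70 = 0.28; difference 0.08.
- p̄ = 0.32; SE₀ = √(2 × 0.32 × 0.68/65) = 0.0818; SE₁ = √((0.36 × 0.64 + 0.28 × 0.72)/65) = 0.0815.
- Φ[(0.08 − 1.96 × 0.0818)/0.0815] ≈ 0.16.

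| True risk, both arms | Detection | Observed | Spurious difference | Chance of false significance in that direction |
|---|---|---|---|---|
| 20% | 90% v 80% | 18% v 16% | 2 points | 5% |
| 20% | 90% v 70% | 18% v 14% | 4 points | 9% |
| 40% | 90% v 80% | 36% v 32% | 4 points | 7% |
| 40% | 90% v 70% | 36% v 28% | 8 points | 16% |
| 60% | 90% v 80% | 54% v 48% | 6 points | 10% |
| 60% | 90% v 70% | 54% v 42% | 12 points | 28% |

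With equal detection the difference is zero and the chance is the nominal 2.5%. Either arm could be the one with fuller detection.

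**The case against.** The case on the other side has real weight.

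- **Mitigation is built in.** Each listed event is prompted, which limits dependence on the caller. Both arms get the same number and timing of calls. Medical records are a source independent of the caller. Home weights, taken at least every 3 weeks, do not depend on who phones. All of this stands and makes the problem smaller, but it does not put the same role on the phone in both arms.
- **The blinding sentence may mean only the scheduled assessments.** Outcomes are said to be measured at baseline, after chemotherapy and at 2 years, and the blinding section goes on to physiological outcomes. That reading is plausible. The text does not say it, however, and the heading Safety outcomes points the other way. A clarifying clause would settle it.
- **No between-arm safety test is stated.** Correct. The concern applies to any arm-wise summary, tested or not.
- **The illustration is all assumption.** Also correct. It shows what unequal detection could do, not what it will do.

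Three stronger readings are tempting and are not supported:

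- A reader might infer that the dietitian judges whether events were caused by the dietitian's own intervention. The article says that participants are probed on grade and origin. It does not name who assigns either, and it has study investigators assess safety case by case.
- A reader might infer that the call-collected events are the main safety evidence because there is no data safety monitoring committee. The other sources above contradict the first part, and a committee would not change who elicits events.
- A reader might infer that the safety comparison is biased. Neither the existence nor the direction of unequal elicitation is documented.

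**Conclusion.** The concern holds as a risk of differential ascertainment and as an inaccurate blinding statement. Caller role is fully confounded with arm and both callers are aware of allocation, so the unqualified assessor-blinding claim does not hold for call-collected adverse events. A between-arm summary of those events would not be strictly comparable.

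Size and direction are unknown. On assumed true risks of 20% to 60% and detection of 90% against 70% to 80%, the spurious difference runs from 2 to 12 points; with equal detection it is zero. Whether the coordinator's calls use the same probing for grade and origin is not explicit. The primary MRI outcome and the laboratory outcomes are not touched. This should be corrected, but it does not threaten the trial's main result.

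**What to change.** 1. Use the same scripted CTC-AE checklist through one channel in both arms at the existing call times, and make it the source for the between-arm comparison. The channel could be a participant-completed electronic form, or the same staff role asking in both arms. The dietitian's own call notes would not feed that comparison.
2. Where existing staff allow, have grade and origin assigned from that form, with the arm masked, by someone who does not deliver the intervention. This is desirable, but the fix works without it.
3. Present call-collected and medical-record events separately by arm.
4. Restrict the blinding statements in Study design, randomisation and blinding and in the Discussion to the outcomes they cover, and say that call-collected adverse events are not assessed blind.

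The cost is a small amendment, one short form and slight participant burden. Masked grading may need extra staff time across two sites, which is why it is conditional. Because participants are unblinded, some reporting bias will remain.
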